### Blinding

The study will be conducted as a blinded trial. Patients, treating physicians and nursing staff will be unaware of the treatment allocations. To maintain blinding of these trial team members, some of the trial staff will be unblinded; specifically, the study pharmacist and the trial statistician.

The study pharmacist will prepare either the study drug or the placebo solution, according to the randomisation schedule. The infusions will be prepared in the aseptic unit on the morning of surgery and will be dispatched to the PACU to be commenced within 1 h of extubation. Both study drug and placebo solutions will appear identical: clear in colour, packaged and labelled identically by the trial pharmacist.

Procedures will be put in place for emergency unblinding. The blinding can be broken in the event of a serious adverse event (SAE) or at request of the treating clinician to the study principal investigator (PI), due to clinical need. In the event of an allergic reaction where the allergen is unclear, even though the incidence of anaphylactic reaction to naloxone is rare, the study infusion should be stopped immediately and the treatment allocation of the patient will be unblinded.

For the purposes of emergency unblinding, a copy of the randomisation schedule will be stored in sequentially numbered opaque sealed envelopes (labelled with randomisation codes), in a cupboard in the administration office of the intensive care unit (ICU), in very close proximity to PACU. The PI and ICU nursing managers will be aware of the location of the randomisation schedule in the event of an emergency.

The study PI will know the location of the subject randomisation codes and will be contacted in any emergency situation to assist with unblinding the allocation. The contact details for the PI will be recorded in the clinical notes and on the anaesthetic sheet in the clinical notes. Nursing staff will be made aware of the location of these contact details during handover of the patient from the operating theatre.

When final database entries have been made and final queries have been resolved, the study database will be locked. A blind review of the data will take place, prior to final data analysis. For the blind review, the study statistician will receive the study dataset with the absence of patient randomisation codes, and with treatment arms labelled but not identified. The purpose of the blind review will be to assess data for protocol violations, to check for outliers, to determine whether variable transformations are appropriate and to decide whether the planned statistical analysis is appropriate. The blind review will inform the final plan for analysis.

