### Randomisation

Trial treatment will be allocated between study drug and placebo in a ratio of 1:1 according to variable block randomisation, with block sizes of 4 and 6. The randomisation schedule will be drawn up by a trial statistician using the statistical software R (R Core Team, 2016). The randomisation schedule will consist of a list of randomisation codes, each with a corresponding treatment assignment.

Randomisation will be implemented by the study pharmacist. All eligible consenting patients will be randomised on the morning of surgery. The treating clinician will assign each patient a randomisation code and will inform the study pharmacist of this code. The study pharmacist will use the pre-prepared randomisation schedule to determine treatment allocation of a patient (study drug or placebo) according to the patient’s randomisation code. They will not inform the treating physician, nursing staff or allocated patient.

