### Primary outcome analysis

The primary outcome will be summarised as the number and percentage of patients in each treatment arm who develop respiratory depression within the study period. Percentages will be calculated using the number of patients for whom data are available as the denominator. Denominators will also be reported.

Risk of respiratory depression will be compared across treatment arms using a risk ratio with an associated 95% CI.

The primary analysis will test the superiority hypothesis that the risk of respiratory depression is reduced for patients receiving a prophylactic naloxone infusion, compared to patients receiving a placebo infusion. The primary outcome will be modelled as a binomial random variable, using a one-sided, two-proportion Z test, with continuity correction.

Sensitivity analysis of the primary outcome will be conducted using logistic regression modelling, adjusting for potentially relevant covariates, to determine whether the estimated treatment effect differs after covariate adjustment. Potentially relevant covariates to be considered include:AgeBMI (Body Mass Index), Duration of surgeryDuration of study infusionTime from injection of ITM to end of studyDose of intraoperative intravenously administered fentanylDose of postoperative intravenously administered fentanyl

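### The blind review that feeds the final analysis plan uses outcome data split by arm, so a change made there could not be shown to be independent of the result

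*Protocol article*

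**What the plan says.** The last paragraph of the Blinding section of the protocol article sets out a sequence. The database is locked. Then "A blind review of the data will take place, prior to final data analysis". For that review, "the study statistician will receive the study dataset with the absence of patient randomisation codes, and with treatment arms labelled but not identified". Its purposes are to look for protocol violations and outliers, to consider transformations, and "to decide whether the planned statistical analysis is appropriate". The paragraph ends: "The blind review will inform the final plan for analysis".

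Three other places bear on this:

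- **Primary outcome analysis** specifies the primary test, "using a one-sided, two-proportion Z test, with continuity correction", and makes covariate-adjusted logistic regression a sensitivity analysis with seven candidate covariates.
- **Statistical analysis plan** makes a modified intention-to-treat set the main set, excluding only patients who withdrew consent, and adds a per-protocol analysis.
- **Randomisation** and the start of **Blinding** deal with who knows the allocation: "The randomisation schedule will be drawn up by a trial statistician", and "some of the trial staff will be unblinded; specifically, the study pharmacist and the trial statistician".

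**The concern.** A blind review exists so that the trial can later show that its analysis decisions were made without knowledge of the result. That requires data from which the treatment comparison cannot be made. Here each patient carries an arm label, so any outcome, including the primary one, can be tabulated by arm. The reviewer can see how large the difference is and how an alternative analysis would change it. Only the names of the arms are withheld.

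The review also has authority over the analysis: it judges whether the plan is suitable and feeds the final version. If it led to a different test, a different handling of violations or a particular covariate set, the trial could not demonstrate that the choice was independent of the difference on view, however well motivated it was. The defence of a confirmatory p value rests on that demonstration.

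**Working it through.** **Step 1. The design figures.** Inputs from Sample size and power: placebo risk p1 = 0.31; 75% reduction, so p2 = 0.31 × 0.25 = 0.0775; one-sided 5%; power 80%; continuity correction.

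- Mean risk = (0.31 + 0.0775)/2 = 0.19375; difference d = 0.2325.
- Uncorrected n = [1.645 × √(2 × 0.19375 × 0.80625) + 0.842 × √(0.31 × 0.69 + 0.0775 × 0.9225)]² / 0.2325² = 34.7.
- Corrected n = (34.7/4) × [1 + √(1 + 4/(34.7 × 0.2325))]² = 42.8, so 43 per group, 86 in total, as stated.
- Dropout: 86/0.9 = 95.6, so 96, or 48 per group, as stated.

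The figures used below are therefore the plan's own.

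**Step 2. How well do unnamed labels mask the arms?** Let X be the number of placebo patients with respiratory depression, Binomial(48, 0.31), and Y the number on naloxone, Binomial(48, p2). The expected counts under the assumed effect are 48 × 0.31 = 14.9 and 48 × 0.0775 = 3.7, about 15 v 4. Summing the joint probabilities over all pairs with Y < X gives:

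| True naloxone risk | Source | P(fewer events on naloxone) |
|---|---|---|
| 7.75% | plan's 75% reduction | 0.998 |
| 15.5% | assumption: 50% reduction | 0.956 |
| 31% | no effect | 0.456 (tie 0.088) |

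If naloxone works as the plan assumes, or even at a 50% reduction, the arm with fewer events is almost certainly naloxone. With no effect, this outcome alone does not reveal which arm is which, but the size of the difference is still visible.

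**Step 3. What can the review change?** Set the sections side by side:

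| Item | Specified in advance? | Protected from the review? |
|---|---|---|
| Primary test | Yes (Primary outcome analysis) | Not stated |
| Main analysis set | Yes (Statistical analysis plan) | Not stated |
| Covariates for sensitivity models | Candidate list only | Not stated |
| Handling of protocol violations | Assessed at the review | Not stated |

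The primary outcome is dichotomous, so transformations and outlier checks on it do not arise. The routes that could reach the primary analysis are the judgement on protocol violations and the judgement on whether the planned analysis is suitable.

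**Step 4. Can the effect on the type I error be sized?** With 31% risk in both arms and 48 per arm, exact enumeration gives a one-sided rejection rate of 3.2% for the planned corrected test and 5.1% for the uncorrected test. Dropping the correction after a look at the data would thus use up the conservatism of the planned test and bring it to about the nominal 5%. Going further means assuming which alternative analyses would be tried, how the covariates behave and which patients would be excluded. The article supplies none of these, so no inflation figure follows from it.

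**The case against.** The strongest reply is that the analysis is not open. The primary test is named down to its continuity correction, the main set is defined, the adjusted model is labelled a sensitivity analysis, and the review is described as a check on a plan that already exists. The patient randomisation codes are stripped from the dataset. A full analysis plan, not shown, may limit what the review can alter. All of this stands, and it rules out several stronger readings that a reader might infer:

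- **That the primary analysis will be chosen after the result is seen.** The article specifies one beforehand. What is missing is a statement that it cannot be changed at this review.
- **That the false-positive rate rises by a known multiple.** Any such multiple depends on alternative analyses that the reader supplies. It is also flattered if measured against the planned test's conservative 3.2% rather than the nominal 5%.
- **That the reviewer is the unblinded statistician.** The Randomisation section speaks of a trial statistician and the start of Blinding of the trial statistician, whereas the review paragraph speaks of the study statistician. These may be one person or two. Withholding arm names from someone who already knew them would serve no purpose, which suggests either a second person or loose wording.
- **That the blinding of the trial is undermined.** The review follows database lock. The masking of patients, physicians and nurses, and the recording of outcomes, are not touched.

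The reply does not answer the central point. The review paragraph gives authority over the final plan to someone holding arm-split outcomes, and nothing shown takes the primary analysis out of its reach.

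**Conclusion.** The point holds as a defect in the review procedure. A review on arm-labelled data is not blind to the treatment difference, and under the plan's own effect assumption the labels would be decoded with probability about 0.998 by anyone expecting benefit. That figure rests on independent binomial counts at 31% and 7.75% with 48 per arm. Because the review informs the final plan, any change it makes to the test, the exclusions or the covariates could not be shown to be independent of the result. If nothing is changed, the pre-specified primary test keeps its properties.

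The size of any type I error inflation cannot be derived from the document. The conclusion does not depend on such a figure, nor on who the reviewing statistician is.

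**What to change.** Amend the review paragraph before database lock:

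1. Carry out the blind review on pooled data with the arm column removed, and limit it to data quality, classification of deviations and pooled distributions.
2. State that the primary test in Primary outcome analysis and the main analysis set in Statistical analysis plan stand and are not open to change at the review.
3. Sign off the covariates and any other analysis choices before arm-labelled data are released.
4. Reconcile the Randomisation and Blinding sections on whether the study statistician is the trial statistician listed as unblinded. If so, that person should not make data-dependent changes to the plan.

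The cost is a paragraph of wording and one column fewer in the data export. The reviewer loses some information, since arm-specific distributions would not be visible at that stage. No patients are added.

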#### Data management

Data as outlined above will be collected by the on-site investigators from the postoperative care records. This will be recorded on a data sheet, and transferred to an electronic Case Report Form (CRF). Data reported on the CRF that are derived from source documents must be consistent with the source documents or the discrepancies must be explained. The clinical study monitor and representatives of the regulatory authority can directly access source documents for comparison of data therein with the data in the electronic CRFs and can verify that the study is carried out in compliance with the protocol and local regulatory requirements.

The full dataset should be recorded for all enrolled patients. The investigators will adhere to national and hospital protocols on data use and storage. All paper records will be kept in a locked file cabinet. Research participant data will be stored also on a dedicated, protected research electronic database. The information entered into the electronic database will be stored by the sponsor responsible for the CRF. This server has managed access and password protection. All reads and writes to the database will be recorded with date, time and user. Users will have a unique internal identification and data entry will require an electronic signature which consists of system password and username. A quality assurance audit may be conducted by the sponsor or its agent at any time during, or shortly after, the study.

#### Confidentiality

The trial staff will ensure that the subjects’ anonymity is maintained. The subjects will be identified only by initials and a subject’s identification number on the CRF and any database. All documents will be stored securely. The study will comply with the Data Protection Act.

### Statistical analysis plan

A Consolidated Standard of Reporting Trials (CONSORT) flow diagram will be generated to illustrate the flow of patients through the trial. This will show the number of patients reviewed for eligibility, how many were ineligible, reasons for ineligibility, the number consented, the number randomised and treated and the differences between groups. It will also show the number of patients with adverse events, protocol deviations and any losses to follow-up. The total number of patients analysed in each group will also be shown.

Baseline data, as well as primary and secondary outcomes will be summarised by treatment arm, using descriptive statistics. The following process variables will also be summarised by treatment group using descriptive statistics and compared between treatment groups using *t* tests (or appropriate non-parametric test):Duration of follow-upDuration of surgeryDuration of study infusionTime from injection of ITM to end of studyDose of intraoperative intravenously administered fentanyl

For inferential analysis of primary and secondary outcomes, treatment effect will be considered statistically significant if the obtained *p* value is less than 0.05.

The main statistical analyses of primary and secondary outcomes will be conducted following the modified intention-to-treat (ITT) principle on a full analysis set of patients, excluding those who withdrew consent to participate or have their data used in the study. A further per-protocol analysis will be carried out on all primary and secondary outcomes for patients who received any dose of the study infusion.

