### Setting

The trial will be carried out in the hepatopancreaticobiliary surgery unit of St Vincent’s University Hospital. Participants will be cared for in either the post-anaesthesia care unit (PACU) or the Bloomfield high-dependency unit (HDU) for the duration of the trial period. Nursing care will be at least a ratio of 1:2 for the duration of the trial. All data collected pertaining to the primary and secondary outcomes will be collected as part of the routine postoperative nursing care documentation.

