### Outcome measures

The primary outcome of this trial is the rate of respiratory depression during the study period for patients receiving naloxone infusion compared to placebo. Respiratory depression will be diagnosed based mainly on criteria derived from the American Society of Anesthesiologist’s (ASA) ‘Practice Guidelines for the Prevention, Detection and Management of Respiratory Depression Associated with Neuraxial Opioid Administration’ [40] 2016 document. The criteria we will use are: respiratory rate < 10 and/or a decrease in SpO_2_ to < 92% and/or an increase in FiO_2_ required to maintain SpO_2_ > 92%. The primary outcome will be recorded as a dichotomous variable, recording any episode of respiratory depression during administration of the study infusion. Study infusion will be administered from within 60 min of extubation until 8:00 a.m. on the first postoperative morning.

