### Sample size and power

Sample size was estimated to determine the superiority of the prophylactic naloxone infusion compared to placebo in reducing the rate of respiratory depression. Based on an audit of 29 patient charts in our unit containing information on respiratory depression, the percentage of the target patient population who develop respiratory depression without treatment is estimated to be 31% (95% confidence interval (CI) 14.2–47.9%). This is based on the definition of respiratory depression in the ASA guidelines for prevention of respiratory depression with ITM [40].

A clinically significant difference was defined as a 75% reduction in the percentage of respiratory depression among those on treatment, compared to those on placebo. Given the estimate of 31% for the placebo group, this is equivalent to a clinically significant relative risk of 4 (a four-times greater risk of respiratory depression for patients on placebo, than for those on treatment).

Sample size calculations are based on a superiority hypothesis test of the risk of respiratory depression, formulated with the objective of testing whether the risk of respiratory depression is less for those on treatment than for those on placebo. To achieve a power of 80% for this test at a 5% significance level, a sample size of 43 per group is required or a total sample size of 86. This sample size calculation was calculated based on a one-tailed, two-proportion Z test with continuity correction.

After commencement of the study the sample size was inflated to compensate for an un-anticipated dropout rate of up to 10%. The final sample size is 96 (48 per treatment group).

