#### Safety monitoring

The site monitor will regularly review data on adverse events, protocol deviations, and any occurrence of SAEs. However, we have not employed a data monitoring committee, as the sample size is small, and the intervention is low risk. We are confident that by monitoring adverse events through the sponsor, any safety issues which arise will be addressed promptly. Data on safety and tolerability will be summarised by treatment group using descriptive statistical methods, with 95% CIs where appropriate. Patients with adverse events and/or protocol deviations will be identified and evaluated, using a descriptive analysis, to summarise their baseline characteristics and their treatment experience. All patients who received any amount of study infusion (naloxone or placebo) will be included in the safety analysis.

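### The main analysis set drops patients who withdraw consent to participate even when their outcome is already recorded: an avoidable post-randomisation exclusion that can bias the primary comparison in either direction

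*Protocol article*

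**What the plan says.** The Statistical analysis plan section of the protocol article bases the main analyses of primary and secondary outcomes on a full analysis set under a modified intention-to-treat principle, "excluding those who withdrew consent to participate or have their data used in the study". No time limit is attached to either kind of withdrawal.

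Other sections bear on the same patients:

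- Setting: all primary and secondary outcome data "will be collected as part of the routine postoperative nursing care documentation".
- Data management: "The full dataset should be recorded for all enrolled patients".
- Outcome measures: "The primary outcome will be recorded as a dichotomous variable, recording any episode of respiratory depression during administration of the study infusion".
- Primary outcome analysis: "Percentages will be calculated using the number of patients for whom data are available as the denominator". The only sensitivity analysis named there is covariate-adjusted logistic regression.
- Statistical analysis plan: "A further per-protocol analysis will be carried out on all primary and secondary outcomes for patients who received any dose of the study infusion".
- Safety monitoring: "All patients who received any amount of study infusion (naloxone or placebo) will be included in the safety analysis".
- Sample size and power: after the start of the study, "the sample size was inflated to compensate for an un-anticipated dropout rate of up to 10" per cent, to 48 per group. No reasons and no split by arm are given.

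**The concern.** Withdrawing from participation and withdrawing permission to use data are separate decisions. The second leaves the analyst no choice. The first need not remove anything already recorded, yet the stated rule treats both alike.

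As worded, a patient can be randomised, receive the infusion, have respiratory depression charted, then withdraw from participation and disappear from both numerator and denominator of the primary comparison. The same patient still counts in the safety analysis. The exclusion happens after randomisation and may depend on what happened to the patient on treatment, so the arms compared may no longer be the arms randomised.

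The rule also gains nothing. The primary denominator is already limited to patients with data, so those with no outcome data need no separate exclusion for withdrawal. This is a rule that the article states, not a detail left to a fuller document.

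**Working it through.** **Inputs from the article.** Placebo risk 31%; targeted reduction 75%, so naloxone risk 0.25 × 31% = 7.75%; one-sided 5% level; 80% power; two-proportion Z test with continuity correction; 43 per group, raised to 48 (Sample size and power; Primary outcome analysis).

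**1. Reproduce the stated sample size.**

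Difference d = 0.31 − 0.0775 = 0.2325; mean risk m = 0.19375.

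Uncorrected: n = [1.645·√(2m(1 − m)) + 0.842·√(0.31·0.69 + 0.0775·0.9225)]² / d² = 34.67.

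Corrected: (n/4)·[1 + √(1 + 4/(n·d))]² = 42.84, so 43 per group, 86 in total.

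Allowing for dropout: 86/0.9 = 95.6, so 96. Both stated figures reproduce.

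**2. The plan's test.** With placebo x₁/n₁, naloxone x₂/n₂ and pooled risk p̄:

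z = [(x₁/n₁ − x₂/n₂) − ½(1/n₁ + 1/n₂)] / √[p̄(1 − p̄)(1/n₁ + 1/n₂)], with one-sided p = 1 − Φ(z).

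Worked case, 15/48 against 8/48: p̄ = 23/96 = 0.2396; standard error 0.0871; z = (0.1458 − 0.0208)/0.0871 = 1.435; p = 0.076.

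**3. Remove one patient with an event.** The event counts are illustrative.

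| Placebo | Naloxone | Patient removed | z | One-sided p |
|---|---|---|---|---|
| 15/48 | 8/48 | none | 1.435 | 0.076 |
| 15/48 | 7/47 | one naloxone event | 1.646 | 0.0499 |
| 15/48 | 7/48 | none | 1.700 | 0.045 |
| 14/47 | 7/48 | one placebo event | 1.538 | 0.062 |

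In each pair a single exclusion moves the result across 0.05, in opposite directions.

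**4. Type I error with no true effect.** Exact binomial enumeration, 31% risk in both arms, 48 per arm. Only patients with an event withdraw, in one arm only, with the probability shown. Expected events per arm are 48 × 0.31 = 14.9.

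| Withdrawal probability after an event | Expected patients lost | Loss on naloxone only | Loss on placebo only |
|---|---|---|---|
| 0 | 0 | 3.2% | 3.2% |
| 10% | 1.5 | 5.3% | 1.8% |
| 20% | 3.0 | 8.3% | 0.9% |
| 30% | 4.5 | 12.9% | 0.4% |

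The withdrawal probabilities are assumptions, since the article gives none. The starting value is below 5% because the continuity correction is conservative.

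**5. Losses without events.** Removing four naloxone patients who had no event from the first illustration (15/48 against 8/44) moves p from 0.076 to 0.114. More withdrawals on naloxone alone therefore do not determine the direction; the event status of the withdrawers matters too.

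**The case against.** **Direction.** A reader might infer bias towards naloxone: the drug opposes the opioid, analgesia suffers, and patients with events leave that arm. The article does not support this. It nowhere says that withdrawal is more frequent or more event-linked on naloxone, and patients, physicians and nurses are blinded. The mechanism can also run the other way, because a patient whose analgesia was antagonised may be one whose respiration was protected. This objection stands.

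**Size.** The allowance of up to 10% is not described as consent withdrawal, as treatment-related or as occurring after infusion. Randomisation is on the morning of surgery and the infusion starts only after extubation, so dropouts may include patients never infused. Follow-up ends at 8:00 a.m. the next day. Withdrawals after an event may be few. This also stands, and it rules out treating 10% as the rate of event-linked withdrawal.

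**Scope.** It is tempting to read the rule as deleting anyone whose infusion is stopped. It does not: it concerns withdrawal of consent, and the Blinding section describes stopping the infusion without calling it withdrawal.

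**Contradiction.** It is also tempting to say that Data management contradicts the analysis set. It governs what is recorded, not who is analysed, so both can hold. It shows only that the data should exist. Consent documents, which might define withdrawal more closely, are not in the text at hand.

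**Existing safeguards.** The any-dose analysis could retain infused withdrawers, and the CONSORT diagram and reported denominators would show losses. But the any-dose analysis is labelled per-protocol, is not primary, and does not say whether the consent exclusion applies to it. Covariate adjustment cannot restore excluded patients. These safeguards are partial.

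**Conclusion.** The point holds as a fault in the definition of the main analysis set. Excluding patients who withdraw only from participation is an avoidable post-randomisation exclusion, and it can bias the primary comparison either way. At 48 per arm, one excluded event is enough to change the conclusion when the result lies near the threshold.

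This rests on the literal wording of the rule and on the premise that data already recorded may be kept unless the patient refuses their use. The latter is a general premise that the article does not state. How many patients would be affected, in which arm and with what outcomes cannot be known from the article, so the calculations show sensitivity and do not forecast a bias. Neither a bias favouring naloxone nor the loss of every patient who stops the infusion can be inferred.

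**What to change.** Amend the Statistical analysis plan before database lock:

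- Exclude from the full analysis set only patients who withdraw consent to use of their data.
- Keep all other randomised patients with recorded outcome data in their randomised arm, using data collected up to withdrawal under the existing primary outcome definition.
- Treat routine observations made after the infusion stops, up to 8:00 a.m. and where the patient agrees, as a sensitivity analysis. They fall outside the endpoint window, which covers only the time during the infusion, so they should not enter the primary analysis.
- Record on the case report form which consent is withdrawn and when.
- Report withdrawals by arm with timing and reasons.

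The cost is a revised sentence on the analysis set, a short sensitivity analysis and a case report form item. No extra patients or observations are needed, and the total stays at 96. The small downside is that some patients contribute partial follow-up.

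### The per-protocol set has the same members as the safety set and no adherence criterion, and the sections on the primary outcome disagree about randomised patients who are never infused

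*Protocol article*

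**What the plan says.** All places are in the protocol article.

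- **Statistical analysis plan, main analysis.** It follows the "modified intention-to-treat (ITT) principle on a full analysis set of patients, excluding those who withdrew consent to participate or have their data used". No other exclusion is stated.
- **Statistical analysis plan, second analysis.** "A further per-protocol analysis will be carried out on all primary and secondary outcomes for patients who received any dose of the study infusion".
- **Safety monitoring.** "All patients who received any amount of study infusion (naloxone or placebo) will be included in the safety analysis".
- **Outcome measures.** The opening sentence speaks of the study period, but the operational definition is a yes/no variable "recording any episode of respiratory depression during administration of the study infusion".
- **Primary outcome analysis.** The summary is "the number and percentage of patients in each treatment arm who develop respiratory depression within the study period". It continues: "Percentages will be calculated using the number of patients for whom data are available as the denominator". Denominators will be reported.
- **Randomisation.** "All eligible consenting patients will be randomised on the morning of surgery". Under Investigational product, the infusion starts only after surgery, within an hour of extubation, and runs to 8:00 a.m. the next day.
- **Material for a real per-protocol definition.** Protocol deviations are recorded (Secondary outcomes; Safety monitoring), infusion duration is summarised by arm (Statistical analysis plan), and the Blinding section plans a blind review before final analysis that looks for protocol violations.

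**The concern.** A per-protocol analysis is there to check whether the result holds in patients who were treated and observed as planned. Under the stated rule, a patient whose infusion is stopped after a few minutes, or who has a major deviation, still counts as per protocol. A reader who sees the two analyses agree would take that as evidence of robustness to non-adherence, which the analysis cannot provide.

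The second difficulty concerns patients randomised in the morning who never start the infusion. They belong to the primary set by its definition, yet an outcome tied to the infusion does not exist for them. The sections can be read in three ways: such patients drop out as having no data, count as free of events, or are observed over the study period at untreated risk. The choice changes the primary estimate or its precision, and it should not be made after the data are in.

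**Working it through.** **1. Membership of the sets**

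| Set | Condition for entry | Adherence or deviation criterion | Never-infused patients |
|---|---|---|---|
| Full analysis set (primary) | Consent not withdrawn | None | In |
| Per-protocol | Any dose of infusion | None | Out |
| Safety | Any amount of infusion | None | Out |

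The second and third rows are the same condition in different words. The per-protocol set differs from the primary set only by leaving out never-infused patients. If those patients also leave the primary analysis because they have no data, the per-protocol analysis simply repeats the primary one.

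**2. The outcome window**

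Study involvement ends at 8:00 a.m. (Interventions), which is also the planned end of the infusion. For a fully infused patient the two windows close together, so the difference in wording is harmless. It matters when the infusion is never started: the infusion window is then empty, whereas the study period is not.

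**3. The plan's own figure**

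Inputs from Sample size and power: placebo risk p1 = 0.31; 75% reduction, so p2 = 0.25 × 0.31 = 0.0775; difference d = 0.2325; mean risk 0.19375; one-sided 5% (z = 1.645); 80% power (z = 0.842).

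- Uncorrected: n' = [1.645 × √(2 × 0.19375 × 0.80625) + 0.842 × √(0.31 × 0.69 + 0.0775 × 0.9225)]² / 0.2325² = 34.7, i.e. 35.
- With continuity correction: n = (n'/4) × [1 + √(1 + 4/(n' × d))]² = 42.8, i.e. **43 per group**, as stated.
- Dropout: 86 / 0.9 = 95.6, i.e. **96**, as stated.

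**4. What the three readings do**

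Assumption: a fraction f of each arm of 48 is never infused. The article gives no such figure; f = 10% is used here because it equals the planned dropout allowance. The corrected power approximation is Φ{[d − 1/n − 1.645 × √(2 × p̄ × (1 − p̄)/n)] / √[(p1(1 − p1) + p2(1 − p2))/n]}, where p̄ is the mean of p1 and p2. Exact power sums binomial probabilities over every pair of counts for which the planned one-sided corrected Z test gives p < 0.05.

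| Reading at f = 10% | Placebo risk | Naloxone risk | n per arm | Risk ratio | Approx. power | Exact power |
|---|---|---|---|---|---|---|
| None never infused | 31% | 7.75% | 48 | 0.25 | 84.7% | 86.7% |
| Excluded as no data | 31% | 7.75% | 48 × 0.9 = 43.2 | 0.25 | 80.4% | not computed here |
| Scored as non-events | 0.9 × 31 = 27.9% | 0.9 × 7.75 = 6.98% | 48 | 0.25 | 79.4% | 81.8% |
| Kept at placebo risk | 31% | 0.9 × 7.75 + 0.1 × 31 = 10.1% | 48 | 0.33 | 74.6% | 76.5% |

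Over f = 5%, 10% and 15%, approximate power is 82.7%, 80.4% and 77.8% if they are excluded; 82.2%, 79.4% and 76.3% if scored as non-events; and 80.0%, 74.6% and 68.9% if kept at placebo risk. The 10% inflation of the sample size therefore matches the reading in which these patients leave the analysis, not the one in which they stay at untreated risk.

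**The case against.** The defence has real substance. The primary analysis is openly called modified, and its exclusion is stated. Keeping never-infused patients is what intention-to-treat intends; at untreated risk they pull the estimate towards no effect, which is conservative for a superiority claim. Partial exposure is not ignored either: infusion duration is compared between arms and is a candidate covariate, and the blind review is to inform the final analysis plan. All of this stands, but none of it changes the stated per-protocol definition, which uses neither deviations nor duration. Nor can this be left to an unseen analysis plan as a missing detail, because the article does give a definition and it does not fit its label.

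Four stronger readings may tempt a reader, and the document does not support them.

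- *That neither analysis estimates what it claims.* For the primary analysis this goes too far. Its set is legitimate; what is unresolved is the outcome window and the counting of one group.
- *That deteriorating patients are lost through the available-data denominator.* Any episode counts, so a patient who met the criteria before records ended already has an event. Observations come from routine nursing records at a ratio of at least 1:2, and the full dataset is required for all enrolled patients.
- *That missing outcomes would probably overturn the result.* With 13/43 against 3/43 observed, the planned test gives p = 0.006. Adding five missing patients per arm, with three events on naloxone and none on placebo (13/48 against 6/48), gives p = 0.062. That is an extreme pattern: a single event among the missing placebo patients (14/48 against 6/48) gives p = 0.039, and two naloxone events with no placebo events (13/48 against 5/48) gives p = 0.034. It also treats the whole dropout allowance as missing outcomes, which the article does not say.
- *That the primary set should be narrowed to patients whose infusion was started.* This is a trade-off, not a correction, and the any-dose analysis already covers that population.

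**Conclusion.** The point holds in two parts. First, the per-protocol set is mislabelled: it has the same members as the safety set and cannot test the result in patients treated as planned. This follows from the text alone and needs no assumption. Second, Outcome measures, Statistical analysis plan and Primary outcome analysis conflict on never-infused randomised patients. The size of that problem depends on how many there are, which the article does not give. At an assumed 10% per arm, exact power is 81.8% (non-events) or 76.5% (placebo risk) against 86.7% with none, and only the last reading moves the risk ratio, from 0.25 to about 0.33. If every randomised patient is infused, the second part has no numerical effect.

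No stated figure is wrong: 43 per group and 96 in total both reproduce. The matter is worth correcting before database lock, but it does not invalidate the primary analysis.

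**What to change.** 1. Rename the any-dose set as the treated (safety) set. Its analysis of primary and secondary outcomes can stay, under that name.
2. Define the per-protocol set as the subset without major protocol deviations, with the list of major deviations fixed in advance. Classify patients at the planned blind review with arm labels removed; as now written, that review shows arms labelled though not identified.
3. Reconcile Outcome measures, Statistical analysis plan and Primary outcome analysis by stating one outcome window that applies to every patient in the primary set, and how never-infused patients are counted. One workable version keeps all randomised patients, with a window that ends at 8:00 a.m. whether or not the infusion was given and whose start does not depend on the infusion.
4. Optional: a tipping-point table for unknown outcomes.

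The cost is a few sentences and the classification of deviations at a review that is already planned. No new data and no change in sample size are needed.
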